#### Conditions for Suspension

(1) If an SAE occurs during the study, the trial should stop immediately.(2) If there is a major error in the trial, or a serious deviation of protocol during implementation, which makes it difficult to evaluate the drug efficacy and safety, the trial should be discontinued.(3) If the drug has a poor therapeutic effect or no clinical value during the trial, the trial should be stopped.(4) The sponsor requests to stop the trial.(5) The administrative authority cancels the trial.

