#### Drop-Out Criteria

(1) Participants who develop an allergic reaction or serious adverse event (SAE) would be withdrawn from the trial according to the doctor’s judgment.(2) Participants with other concomitant diseases occurring during the trial, which affected the assessment of efficacy and safety of JZOL.(3) Participants whom have poor compliance, changed their medication midway, or added drugs prohibited under this study.(4) Any reason breaking the double-blind setting of this clinical trial.(5) After medication, if the total score of cough and expectoration increased by four points or the armpit temperature >38.5°C continued for more than 48 h, or the child developed bronchial pneumonia, the tested medication should be stopped immediately, effective treatment should be given. The child should complete all laboratory tests, be withdrawn from the study, and be considered an invalid case.(6) Participants who are found to have serious violations of inclusion or exclusion criteria after being enrolled in this study.

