### Randomization and Blindness

In this protocol, the stratified block randomization method is adopted. Participants will be stratified according to age. The age stratification is divided into five categories, which are 2–3 years old, 4–5 years old, 6–7 years old, 8–12 years old, and more than 12 years old. SAS 9.4 is used to generate random numbers and corresponding treatment groups. Random numbers are assigned by a central random platform (DAS for IWRS), and competitively selected by each clinical subcenter. There are two copies of the random scheme, which were sealed and stored respectively in the sponsor and the designer of the study scheme.

The double-blind method is used in this trial. Participants, clinicians, and outcome evaluators will be blinded. A two-stage blind design also will be used in the study. In this design, the statistical analyst will not know the grouping of medications in the study. Thus, the statistical analyst also will be blinded. To ensure the quality of blinding, all drugs and placebo are required to be uniformly packaged, while guaranteeing that there is no difference between real drugs and placebo in shape, color, sizer, taste, and smell. Entrust a third party to randomly number the corresponding medicines according to the random coding table and paste them in a conspicuous position in the external packaging of the medicines. The researchers logged on to the designed central random platform to obtain the random numbers of participants, and the pharmacy administrators of each clinical unit distributed the corresponding medicines to the patients according to the random number, to ensure that both researchers and patients were blinded. All the outcome measures and statistical analysts were not involved in the implementation of the trial, nor did they know the study design and hypotheses. If the participants experience SAEs during this trial, the principal investigator at each center has the authority to log in to the central randomization platform to unblind the patients, the reason for urgent unblinding should be noted, dated, and recorded on case report form (CRF).

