### Statistical Analysis

SAS will be used for statistical analysis. Intention-to-treat analysis will be carried out in this trial, which refers to the analysis of all cases that have been randomized and used drugs at least once. All statistical tests are conducted using a two-sided test, and *p* <0.05 would be considered statistically significant. The missing data will be filled up by carrying forward the last measured value in this trial. Covariance analysis is used for the evaluation of the cough disappearance time. The group is taken as a fixed effect, and the baseline value of the cough symptom score is taken as covariance into the model for analysis. The difference between the different values of the two groups and their bilateral 95% confidence intervals are calculated. Then, the lower limit of bilateral 95% confidence intervals and the preset non-inferiority standard are compared to determine whether the test group is inferior to the control group. In addition, the subgroup analysis is performed according to age (2–3 years, 4–7 years, and 8–14 years). Measurement methods and data sets of secondary outcomes are shown in Table 5. In terms of safety, the number of AEs and SAEs during the study will be listed, and their incidence will be calculated.

**TABLE 5 T5:** Secondary outcome.

Secondary outcome	Test method	Data set
Time-lapse analysis of measured value and changed value of cough symptom score	T test is used to compare the differences between groups	FAS^a^
AUC of cough and expectoration symptom score - time		
Onset of cough relief		
Clinical recovery time		
Disappearance rate of cough, expectoration and lung rales	χ2 test or Fisher’s exact probability method is used to compare the differences between groups	
Use of antibiotics, antipyretics and analgesics		
Analysis on the curative effect of TCM syndrome	CMH chi-square is used to compare the differences between groups	

a FAS, Full Analysis Set; AUC, Area Under Curve.

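### The trial-level rule that an SAE stops the whole trial is inconsistent with the child-by-child handling of SAEs elsewhere in the protocol

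*Protocol article*

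**What the plan says.** Conditions for Suspension, item 1, reads: "If an SAE occurs during the study, the trial should stop immediately". The list it heads concerns the trial as a whole; its last item, for example, is "The administrative authority cancels the trial". Exits of individual children have their own sections, Drop-Out Criteria and Voluntary Withdrawal of Participants.

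SAEs appear in three other places:

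- Drop-Out Criteria, item 1: "Participants who develop an allergic reaction or serious adverse event (SAE) would be withdrawn from the trial according to the doctor’s judgment".
- Randomization and Blindness: "If the participants experience SAEs during this trial, the principal investigator at each center has the authority to log in" to the randomisation platform and unblind, with the reason recorded on the CRF.
- Statistical Analysis: "the number of AEs and SAEs during the study will be listed, and their incidence will be calculated".

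None of these three mentions a halt of the trial. Sample Size Calculation sets 417 children per group for a power of 0.95, raised to 500 per group and 1000 in total to allow for withdrawals.

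**The concern.** Read as written, one SAE in either arm, related to treatment or not, stops recruitment and treatment at all ten hospitals. The other three provisions leave discretion to the treating doctor or the centre's investigator and describe no consequence beyond the affected child. At the first SAE, staff could follow one text or the other and reach different actions.

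Either course has a cost. If the suspension rule is followed literally, a single unrelated event can end the trial short of its planned size. If it is passed over, the trial departs from its own safety text at the first SAE.

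**Working it through.** **1. The plan's own sample size.** Inputs from Sample Size Calculation: margin 0.5 days, SD 2 days, the same mean in both arms (true difference 0), one-sided alpha 0.025, power 0.95.

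n per group = 2 × SD² × (z0.975 + z0.95)² / margin² = 2 × 4 × (1.960 + 1.645)² / 0.25 = 415.8, rounded up to 416. The exact noncentral-t calculation gives power 0.9496 at 416 and 0.9501 at 417, so the stated 417 reproduces. The evaluable total behind the 95% power is 2 × 417 = 834.

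**2. The passages side by side.**

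| Section | Level | What an SAE leads to | Discretion |
|---|---|---|---|
| Conditions for Suspension, item 1 | Trial | Immediate stop | None stated |
| Drop-Out Criteria, item 1 | Child | Withdrawal | Doctor's judgment |
| Randomization and Blindness | Child | Possible unblinding, recorded on the CRF | Centre's principal investigator |
| Statistical Analysis | Trial report | Count and incidence | Not applicable |

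The first row is the only one with a consequence for the trial. The article does not say how it relates to the other three. The data monitoring committee named in Data Management appears there only in connection with the review of paper records, so that mention does not supply a safety review step.

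**3. How often the literal rule would be triggered.** The protocol gives no SAE rate. Let p be an assumed per-child risk over the study, with children independent. Then:

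- P(at least one SAE in N children) = 1 − (1 − p)^N
- expected number of children enrolled at the stop, capped at 1000 = [1 − (1 − p)^1000] / p

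| Assumed p | N = 1000 | N = 834 | Expected enrolment at stop (capped at 1000) |
|---|---|---|---|
| 0.01% | 9.5% | 8.0% | 952 |
| 0.05% | 39% | 34% | 787 |
| 0.1% | 63% | 57% | 632 |
| 0.2% | 86% | 81% | 433 |
| 0.3% | 95% | 92% | 317 |
| 0.5% | 99.3% | 98% | 199 |

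The 834 column is the kinder one. It counts only as many children as must be evaluable, whereas more would be enrolled to allow for withdrawals (1 − 417/500 = 16.6% if the full allowance is used).

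**4. Thresholds for 1000 children.**

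- Even odds of a stop: p = 1 − 0.5^(1/1000) = 0.069%, or about 1 in 1,440 children.
- A 90% chance of no stop: p = 1 − 0.9^(1/1000) = 0.0105%, or about 1 in 9,500 children.

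**The case against.** Four points can be made in the plan's defence.

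- **Different levels.** Withdrawing a child, unblinding that child and halting the trial can all follow one event. Listing SAEs and their incidence is ordinary reporting language that works for zero, one or more events. This stands as far as it goes: the provisions are not logically impossible together. But the child-level texts read as if the trial continues, and nothing connects them to the trial-level rule.
- **Temporary halt.** The heading speaks of suspension, so a pause pending review may be meant. That is possible. The sentence itself speaks of stopping at once and no restart path is printed. Even a temporary halt of every centre for each SAE would need to be squared with the child-level texts.
- **Low SAE risk.** Medication lasts 7 days, and severe bronchitis, severe organ disease, severe malnutrition and immunodeficiency are excluded. Rates below 0.07% cannot be ruled out from the documents. This stands, and it makes the numerical consequence conditional.
- **Condensed article.** Review and restart procedures may sit in the full protocol. Their absence here is therefore not the complaint. The complaint is that a rule is stated without qualification and then sits beside statements that do not fit it.

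**Conclusion.** The inconsistency is real and does not depend on any SAE rate. The suspension rule needs to be reconciled with Drop-Out Criteria, Randomization and Blindness, and Statistical Analysis. This should be fixed, but it does not touch the margin, the sample size calculation or the primary analysis.

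A reader might infer three stronger things, and the documents do not support them:

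- **That the trial would probably end early or miss 417 per group.** This needs a per-child SAE risk above about 0.07%, and the protocol states none. Across assumed risks from 0.01% to 0.5%, the chance of a stop within 1000 children runs from 9.5% to 99.3%. At 0.1%, about 43% of such trials would pass 834 children without an SAE. All these figures assume independent children and a literal reading of the rule.
- **That the SAE provisions cannot all apply.** They act at different levels, so the fault is inconsistency, not impossibility.
- **That the item on poor therapeutic effect in the same list is a fault of the same kind.** Criticism of it rests on interim detail that an article may leave to the full protocol or the SAP, so it forms no part of this point.

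**What to change.** Reconcile Conditions for Suspension, item 1, with Drop-Out Criteria, item 1, the unblinding text in Randomization and Blindness, and the safety reporting text in Statistical Analysis. One statement should say what an SAE triggers for the child and, separately, what it triggers for the trial. It should also say whether a trial-level action is a temporary halt or a permanent stop. Which events trigger which action is for the sponsor and its safety body to decide; no trigger is proposed here. The cost is a protocol wording amendment, with no added patients, procedures or analyses.

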### Sample Size Calculation

In this study, the disappearance time of cough is used as the primary outcome. According to previous studies, the disappearance time of cough in the experimental group and the control group is about 5 ± 2 days. The non-inferiority threshold of this study is set as 0.5 days, unilateral α = 0.025, power = 0.95, and the PASS (V14.0) is selected to estimate the sample size. Based on the calculation, 417 cases are needed for each group. After considering the proportion of withdrawals, the sample size of this study is 500 cases for each group, with a total of 1000 cases.

### Randomization and Blindness

In this protocol, the stratified block randomization method is adopted. Participants will be stratified according to age. The age stratification is divided into five categories, which are 2–3 years old, 4–5 years old, 6–7 years old, 8–12 years old, and more than 12 years old. SAS 9.4 is used to generate random numbers and corresponding treatment groups. Random numbers are assigned by a central random platform (DAS for IWRS), and competitively selected by each clinical subcenter. There are two copies of the random scheme, which were sealed and stored respectively in the sponsor and the designer of the study scheme.

The double-blind method is used in this trial. Participants, clinicians, and outcome evaluators will be blinded. A two-stage blind design also will be used in the study. In this design, the statistical analyst will not know the grouping of medications in the study. Thus, the statistical analyst also will be blinded. To ensure the quality of blinding, all drugs and placebo are required to be uniformly packaged, while guaranteeing that there is no difference between real drugs and placebo in shape, color, sizer, taste, and smell. Entrust a third party to randomly number the corresponding medicines according to the random coding table and paste them in a conspicuous position in the external packaging of the medicines. The researchers logged on to the designed central random platform to obtain the random numbers of participants, and the pharmacy administrators of each clinical unit distributed the corresponding medicines to the patients according to the random number, to ensure that both researchers and patients were blinded. All the outcome measures and statistical analysts were not involved in the implementation of the trial, nor did they know the study design and hypotheses. If the participants experience SAEs during this trial, the principal investigator at each center has the authority to log in to the central randomization platform to unblind the patients, the reason for urgent unblinding should be noted, dated, and recorded on case report form (CRF).

### Intervention Method

The Intervention group takes JZOL and AHCHOS placebo, while the control group receives AHCHOS and JZOL placebo. Both drugs and their placebos are taken orally. According to different ages and weights, the dosages of the two drugs are shown in Table 1. The conditions treated by the two drugs in this study are the same as publicly available information. Ibuprofen Suspension will be taken when two groups of participants appear in an emergency. The medication lasts for 7 days. The treatment medicine and their placebos are provided by Jiangsu Kanion Pharmaceutical Co., Ltd according to the double-blind principle. The schedule of enrollment, interventions, and assessments is shown in Table 2.

**TABLE 1 T1:** Usage instructions for both drugs.

Jinzhen oral liquid and its placebo		
**Age**	**Dosage**	
2–3 years old	10 ml each time, twice a day	
4–7 years old	10 ml each time, three times a day	
8–14 years old	15 ml each time, three times a day	
Ambroxol Hydrochloride and Clenbuterol Hydrochloride Oral Solution and its placebo		
** Age**	**Weight**	**Dosage**
** 2–3 years old**	12–16 kg	7.5 ml each time, twice a day
** 4–5 years old**	16–22 kg	10 ml each time, twice a day
** 6–12 years old**	22–35 kg	15 ml each time, twice a day
** More than 12 years old**	—	20 ml each time, twice a day

Note: In case of inconsistency between age and weight, the dosage can be adjusted according to their weight.

**TABLE 2 T2:** Flow chart for clinical trial.

Stage procedure	Screening stage /Baseline (1st Visit)	During treatment (2nd Visit)<	After treatment (3rd Visit)
	−1 ∼ 0 days	5 ± 1 day	7 ± 1 day
Patient screening	×	—	—
Sign informed consent form	×	—	—
Fill in demographic information	×	—	—
Past medical history	×	—	—
Medical comorbidities and current medication	×	—	—
Chest radiograph	×	—	—
General examination	×	×	×
Physical examination	×	×	×
TCM syndrome scoring and grading	×	×	×
Routine blood investigations, urinalysis and stool examination	×	—	×
Liver function tests (ALT, ALP, AST, TBIl, γ-GT) and kidney function tests (BUN, Cr)	×	—	×
ECG	×	—	×
Stool/salivary metagenomic analysis	×	×	×
Stool/blood metabolomics analysis	×	×	×
Distribution and withdrawal of the remaining intervention medication	×	—	×
Distribution and withdrawal of patients’ medication diary record cards	×	×	×
Adverse events record	—	×	×
Combination therapy medication record	—	×	×
Conclusion (Trial Summary)	—	—	×

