#### Outcome Evaluation

##### Primary Outcome

The disappearance time of cough should be recorded daily, then evaluated at the study endpoint.

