##### Secondary Outcome

(1) Area Under Curve (AUC) of cough and expectoration symptom score-time, cough symptom score (Table 3), antitussive onset time, clinical recovery time, and TCM syndrome score (Li, 2015) (Table 4) will be daily recorded and evaluated at the study endpoint.i. Cough disappeared: cough symptom score (daytime + night) ≤1 point, and maintained for 24 h or more.ii. Antitussive onset time: the number of days required for cough symptom score to decrease by one point after taking the medicine.iii. Clinical recovery: cough, expectoration and pulmonary symptoms are all mild after treatment, without affecting study, living and sleep.iv. Evaluation criteria for the efficacy of TCM syndromesA. Clinical recovery: the total score decreased by ≥90%.B. Significant effect: the total score decreased by ≥70% and <90%.C. Effective: the total score decreased by ≥30% and <70%.D. Ineffective: those who fail to meet the above standards.(2) The disappearance rate of cough, sputum and pulmonary rales will be evaluated at the study endpoint.(3) The usage of antibiotics, antipyretics or analgesics will be evaluated at the study endpoint.

**TABLE 3 T3:** Cough symptom scoring.

Score	Daytime symptom	Night symptom
0	No cough	No cough
1	Short occasional cough	Short occasional cough during sleep
2	Frequent cough, daily activities mildly affected	Slight disturbance of sleep due to cough
3	Frequent cough, daily activities severely affected	Severe disturbance of sleep due to cough

**TABLE 4 T4:** Quantitative Grading evaluation for TCM syndrome.

Grading symptoms		(−)	(+)	(++)	(+++)
Primary symptoms		0	1	2	3
Cough	Daytime	No cough	Short occasional cough	Frequent cough, daily activities mildly affected	Frequent cough, daily activities severely affected
	Night	No cough	Short occasional cough during sleep	Slight disturbance of sleep due to cough	Severe disturbance of sleep due to cough
Expectoration	Daytime	No expectoration	Phlegm is whitish and slightly sticky	Phlegm is whitish/yellowish and sticky	Phlegm is yellowish and sticky
	Night	No expectoration	Phlegm is easy to cough out	Phlegm is slightly difficult to cough out	Phlegm is difficult to cough out
Secondary Symptoms		0	1	2	3
Fever (24 h maximum axillary temperature)		≤37.2°C	37.3–37.9°C	38.0–38.5°C	>38.5°C
Thirsty		No	Yes	Yes	Yes
Facial Erythema		No	Yes	Yes	Yes
Dysphoria		No	Yes	Yes	Yes
Scanty dark-colored urine		No	Yes	Yes	Yes
Dry stool		No	Yes	Yes	Yes
Tongue and pulse condition		Normal	Abnormal	Others	

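### Table 2 lets the final, after-treatment visit fall on day 6, inside the visit 2 window and before seven full days of a 7-day course (minor)

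*Protocol article*

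**What the plan says.** The Intervention Method section states: "The medication lasts for 7 days". Table 2, in the same section, places visit 2 (the during-treatment column) at 5 ± 1 day. The last column, headed "After treatment (3rd Visit", is at 7 ± 1 day. That last visit is marked for "Distribution and withdrawal of the remaining intervention medication", for handing in the "medication diary record cards", and for "Conclusion (Trial Summary". No later contact is listed.

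The Primary Outcome section says: "The disappearance time of cough should be recorded daily, then evaluated at the study endpoint". It gives no calendar day for that endpoint. The definition of disappearance stands under Secondary Outcome: "cough symptom score (daytime + night) ≤1 point, and maintained for 24 h or more". Also under Secondary Outcome: "The disappearance rate of cough, sputum and pulmonary rales will be evaluated at the study endpoint". Safety Evaluation places the laboratory tests and ECG at baseline and at the close of the trial. Mechanism Investigation takes samples before treatment, at day 5 and when treatment ends. Table 2 puts the last of each at visit 3.

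**The concern.** The two windows share day 6, so a single day counts as both during and after treatment. It also comes before seven full days of the course, whichever day dosing starts.

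Two things follow for children who keep to the schedule. First, the diary that supplies the primary outcome can stop on day 6, 7 or 8. The 24-hour rule makes the last day matter: if the event is dated at the first low score, a diary ending on day c can confirm disappearance only up to about day c − 1. Second, rales, laboratory tests, ECG and the final samples can be taken before treatment has ended. The day-5 and final samples can even fall due on the same day, because no minimum gap is stated.

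This is a stated schedule that conflicts with the stated course length and the column label, not a detail that an article leaves out. A later analysis plan can choose a cut-off, but it cannot recover diary days that were never recorded.

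**Working it through.** **Windows.** 5 ± 1 gives days {4, 5, 6} and 7 ± 1 gives days {6, 7, 8}; the common day is {6}. The article does not say on which day dosing starts. If on day 0, a day-6 visit follows six full days and falls on the seventh dosing day. If on day 1, it follows five full days with the sixth in progress. Neither reaches seven full days.

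**Inputs.** Sample Size Calculation gives 5 ± 2 days in both groups, a 0.5-day margin, one-sided α = 0.025 and power 0.95. Reading the 2 as a standard deviation, n per group = 2 × (1.960 + 1.645)² × 2² / 0.5² = 416, against 417 stated, so that reading is right. The sample size is not affected by this point.

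**Assumptions, not in the article.** Times are normal (log-normal with the same mean and SD in brackets), and the event is dated at the first low score. Unresolved children are scored at their last diary day c. One row of the second table uses c − 1 instead.

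**Share with a confirmable date.** A diary ending on day c confirms times up to c − 1, so the share is Φ((c − 1 − 5)/2).

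| Diary ends | Confirmable | Not confirmable |
|---|---|---|
| Day 6 | 50.0% (57.6%) | 50% (42%) |
| Day 7 | 69.1% (74.7%) | 31% (25%) |
| Day 8 | 84.1% (85.7%) | 16% (14%) |

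Averaged over visits:
- All on day 7: 69.1% (74.7%).
- 10/80/10 on days 6/7/8: 0.1 × 50.0 + 0.8 × 69.1 + 0.1 × 84.1 = 68.7% (74.1%).
- One third each: 67.8% (72.7%).

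The symmetric window therefore costs 0.4 to 1.3 percentage points (0.6 to 2.0).

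**Shrinkage of a true 0.5-day difference.** Without the 24-hour rule, E[min(T, c)] = μΦ(z) − σφ(z) + c(1 − Φ(z)), with z = (c − μ)/σ. For c = 7:
- μ = 5, z = 1: 5 × 0.8413 − 2 × 0.2420 + 7 × 0.1587 = 4.833.
- μ = 5.5, z = 0.75: 5.5 × 0.7734 − 2 × 0.3011 + 7 × 0.2266 = 5.238.
- The difference is 0.404 days.

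The same formula gives 0.323 for c = 6 and 0.457 for c = 8. With the 24-hour rule, z becomes (c − 1 − μ)/σ, and the last term uses the score given to unconfirmed children, c or c − 1. The extra loss is the day-7 difference minus the weighted average over days 6, 7 and 8. For one third each without the 24-hour rule it is 0.404 − (0.323 + 0.404 + 0.457)/3 = 0.009.

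| Scoring | Difference at c = 6, 7, 8 | Extra loss, 10/80/10 | Extra loss, one third each |
|---|---|---|---|
| No 24-hour rule, scored at c | 0.323, 0.404, 0.457 | 0.003 (0.003) | 0.009 (0.009) |
| 24-hour rule, scored at c | 0.324, 0.416, 0.472 | 0.003 (0.003) | 0.012 (0.011) |
| 24-hour rule, scored at c − 1 | 0.225, 0.323, 0.404 | 0.002 (0.003) | 0.005 (0.011) |

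The range for symmetric windows is 0.002 to 0.012 days. A lopsided mix, one third on day 6 and two thirds on day 7, would give about 0.02 to 0.03 days; nothing in the article suggests such a mix.

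**The case against.** A ±1-day tolerance is ordinary, and any two visits two days apart will touch under it. The column label, the 7-day course and the timing of the last samples all show that visit 3 is meant to follow treatment. With first dosing on day 0, which Table 2's baseline of day −1 to 0 allows, the shortfall on day 6 is only part of a day. Tests or an ECG taken that little early matter little for safety, since new abnormalities are re-examined.

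Most of this stands, and it limits the point to a minor one. It does not remove the overlap, because the printed window still permits a visit that contradicts its own label.

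Three stronger readings are tempting and are not supported:
- **Children lose treatment.** A reader might infer that a child seen on day 6 stops early. The drug-return row makes this possible, but nothing tells sites to end dosing early.
- **The window costs 19 points.** The gap between 50% and 31% unconfirmed compares a child seen on day 6 with one seen on day 7. The 31% comes from short follow-up and the 24-hour rule, not from the window. The figures also depend on convention: if times are rounded to the nearest recorded day, the day-6 share is 40%.
- **The comparison is biased.** The same window applies to both blinded arms, so nothing favours one of them. Shrinkage towards no difference is the unwelcome direction for a non-inferiority test, but 0.012 days is 2.4% of the 0.5-day margin.

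**Conclusion.** The point holds as a minor, cheap improvement. The overlap on day 6 and the conflict with a 7-day course follow from Table 2 under either day count. That the diary closes at visit 3 is an inference, though a sound one: the cards are handed in then, the trial concludes, and no common cut-off is stated.

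The consequence is unequal follow-up and noise shared by both arms. For a symmetric window it amounts to 0.4 to 1.3 percentage points of confirmable dates under the normal assumption (up to 2.0 under the log-normal) and 0.002 to 0.012 days of extra shrinkage. These sizes rest on the assumed distribution, on dating the event at the first low score, and on an assumed score for unresolved children. How those children should be scored is a separate question.

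**What to change.** Count the first dose as day 0 and set visit 3 at day 7 + 1 (days 7–8, after the last dose). This removes the overlap with visit 2 and puts every end-of-treatment reading and sample after treatment. Use one diary cut-off, day 8, for every child whatever the visit date, with the day-8 entry taken by telephone if the visit is on day 7. Keep the ban on other cough medicines (Guidelines for Drug Combination) in force until that entry; otherwise it may reflect new treatment.

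Disappearance up to day 7 can then be confirmed for everyone. Under the normal assumption the confirmable share rises from about 68–69% to 84% (log-normal: from about 73–75% to 86%). Most of that gain comes from the longer diary rather than from closing the window.

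The cost is an edit to one column of Table 2, a sentence in the outcome section and a line in the concomitant-medication rules. In practice, booking has two days instead of three, visits may fall out of window more often, and some families get a short call. The day-8 entry is an off-drug day, which the outcome definition should acknowledge.
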